### Secondary endpoints

Time consumption in seconds and thus speed to complete the mobility route will be measured as a secondary endpoint. Investigators measure the time spent by participants to complete the route, and faster speeds indicate improved outcome as long as correct target identification has not been reduced.

Several other secondary endpoints will be used in the study. Visual functions will be estimated using the following five tests:

The National Eye Institute Visual Functioning Questionnaire-25 (VFQ-25), which is a questionnaire for measuring vision problems and concerns associated with a person’s visual function [7,8]. It has been shown that the VFQ-25 is a reliable and valid 25-item version of the 51-item National Eye Institute Visual Function Questionnaire (NEI-VFQ). The VFQ is useful in clinical trials where interview length is a consideration [9]. The VFQ-25 consists of 25 questions related to a person’s activities in daily life.Test of Attentional Performance (TAP) Test 2.3 Visual Field will be used to test for visual field defects. During the test a participant must respond quickly to stimuli in a circumscribed area of the visual field (eg, whenever a flicker stimulus is presented at varying intervals). This happens while participants are engaged in a simultaneous central task to ensure that participants fixate on the middle of the screen throughout the entire test run. When the peripheral stimulus appears, the patient should press the reaction key as quickly as possible [10].Behavioral Inattention Test will be used to assess attention and vision among participants [11]. Also known as Rivermead Behavioral Inattention Test, it is a battery of short tests to assess the presence and the extent of visual neglect on everyday problems faced by persons with visual inattention.  Rey-Osterrieth’s complex figure test will be used but limited to copying an advanced visual figure (without recall) [12]. Rey-Osterrieth’s complex figure test is a well-known neuropsychological assessment in which participants are asked to reproduce a complicated drawing by copying it freehand. Many different cognitive abilities are needed for a correct performance, and the test therefore permits the evaluation of different functions, for example visuo-spatial abilities, attention, planning, and executive functions [12]. The King-Devick Saccade Test will be used as to estimate eye movement disorders, especially a participant’s ability to perform saccades and horizontal eye movements [13].

Cognitive abilities will be measured by the Montreal Cognitive Assessment (MoCA), which is a cognitive screening test providing an estimate of the intellectual functional level [14]. Originally the MoCA was designed as a short screening instrument for mild cognitive dysfunction and dementia. MoCA assesses cognitive domains, for example: attention, executive functions, working and long-term memory, language and visuo-constructional skills [14]. A score of 26 to 30 is considered normal, while lower scores may indicate cognitive dysfunction.

Participants will be screened for potential psychiatric and psychological disturbances as depression and debilitating fatigue using the following 3 questionnaires:

The Major Depression Inventory will be used to measure and estimate symptoms of depression, which have been present for the last 2 weeks. It is a 12-item self-report mood questionnaire, which was developed by the World Health Organization’s Collaborating Center in Mental Health [15].The Fatigue Severity Scale is a 9-item self-administered questionnaire originally developed for measurements of fatigue in multiple sclerosis and systemic lupus erythomatosus. Each item is scored from 1 to 7 with higher scores reflecting increased levels of fatigue. In a recent study, investigators found more valid results if items 1 and 2 were excluded [16]. We refer to the reduced form as FSS-7 and will use the FSS-7 instead of the FSS to estimate fatigue in participants.The Multidimensional Fatigue Inventory 20 (MFI-20), which is a 20-item self-administered questionnaire designed to measure 5 fatigue domains: general fatigue, physical fatigue, reduced activity, reduced motivation, and mental fatigue, will be performed. The MFI-20 general fatigue domain can be used as an overall measure of fatigue, and a score of 12 or more may indicate presence of debilitating fatigue [17-19].

Quality of life will be estimated using the European Quality of Life–5 Dimensions questionnaire (EuroQol-5D) with the health status from each subscale of the EuroQol-5D transformed into a single value by the use of population-based preference weights for Denmark [20]. The EuroQol-5D is applicable to a wide range of health conditions and treatments and provides a simple descriptive profile and a single index value for health status in participants. EuroQol-5D is designed for self-completion by participants and is ideally suited for use in clinics, and in face-to-face interviews [20].

For assessment of invalidity and ability to perform activities of daily living, the modified Barthel-100 Activities of Daily Living Index score will be used with scores ranging from 0 to 100. A score of 100 indicates no problems in general daily living activities, such as mobility, eating, personal hygiene, dressing and toilet use [21].

Furthermore, as part of the study, it will be assessed whether persons with lesion of right hemisphere (ie, left-field hemianopia) may be more likely to be disorientated and due to neglect will overlook more details - this is done by comparing trial participants with right vs. left hemispheric lesions.

### Blinding

Participants are not randomized as there is only an intervention group and no controls. As far as possible, it is ensured that the investigator who measures the subjects' functional level at the end of intervention has not previously had contact with, or knowledge of, the particular participant. Thus, the level of function of participants is evaluated by different persons before and after intervention to ensure impartial assessments.

### Sample Size Estimation

The primary endpoint is the ability to identify the highest number of correct targets on the mobility route test. Based on unpublished pilot data, we expect participants to correctly identify 40% of the mobility targets at baseline, and to be able to identify 65% of correct target 6 weeks after ending the Neuro Vision Technology course. As a basis for power calculation, alpha = .05 and beta = .2 are used. Sample size is calculated to 23 participants. Due to age, difficulty in transport, and the time-consuming intervention, up to 25% dropouts are expected. Thus, we aim to include 29 participants with permanent visual impairment after brain damage corresponding to hemianopia, quadrant hemianopia or scotoma resulting in functional impairment at activity or participation level.

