**Results:**

Funding was provided in June 2017. Results are expected to be available in 2020. Sample size is calculated to 23 participants. Due to age, difficulty in transport, and the time-consuming intervention, up to 25% dropouts are expected; thus, we aim to include at least 29 participants.

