## Results

Funding was provided in June 2017. Results are expected to be available in 2020. Sample size is calculated to 23 participants. Due to age, difficulty in transport, and the time-consuming intervention, up to 25% dropouts are expected; thus, we aim to include at least 29 participants.

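### Enrolling 29 does not keep the required 23 evaluable participants at the plan's own 25% dropout ceiling; the usual calculation gives 31 (minor arithmetic error)

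*Protocol article*

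**What the plan says.** The Sample Size Estimation section of the protocol article expects participants to identify 40% of targets at baseline and 65% six weeks after the course, with "alpha = .05 and beta = .2 are used", and arrives at 23 participants. It then says "up to 25% dropouts are expected. Thus, we aim to include 29 participants". The Abstract (Results paragraph) gives the same base, "Sample size is calculated to 23 participants", with the same dropout allowance. The later Results section words the target as "up to 25% dropouts are expected; thus, we aim to include at least 29 participants". The Abstract also gives 29 as a minimum; only the Methods text gives it as a plain target.

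The Statistical Analysis section leaves incomplete data out of the calculations and tolerates missing data provided that the primary endpoint can still be assessed. The article describes no replacement of participants who drop out.

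**The concern.** All three places present 29 as the result of two inputs: 23 required and a dropout of up to 25%. A dropout percentage applies to those who enter the trial, so the check is whether 75% of the enrolled number is at least 23. For 29 it is not.

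The primary comparison is before versus after in the same person. A participant with no post-course mobility test therefore adds nothing to it, and the number who can be retested is the analysed sample. If dropout reaches the level that the plan allows for, the trial falls below its own required number and so slightly below its stated 80% power. The Limitations section says that eligible patients are hard to find, so accidental over-recruitment is not a safe way to close the gap.

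**Working it through.** **Inputs** (Sample Size Estimation; repeated in the Abstract and Results)
- Required evaluable number: n = 23.
- Dropout ceiling: d = 0.25.
- Stated enrolment target: N = 29.

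**Step 1: reproduce the stated figure.**
- n x (1 + d) = 23 x 1.25 = 28.75, rounded up to 29. This matches.
- n / (1 - d) = 23 / 0.75 = 30.67, rounded up to 31. This does not match.

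The article gives no formula, so multiplication by 1.25 is an inference. The steps below do not depend on it.

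**Step 2: what 29 leaves.**
- Expected completers at 25% dropout: 29 x 0.75 = 21.75.
- In whole participants: 7 losses are 7/29 = 24.1%, within the ceiling, and leave 22. Eight losses are 8/29 = 27.6%, above it. The worst case that the plan allows is therefore 22.
- Losses that still leave 23: 29 - 23 = 6, and 6/29 = 20.7%.

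**Step 3: what target holds at 25%.**
- 30 x 0.75 = 22.5, below 23.
- 31 x 0.75 = 23.25, at least 23.

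The usual calculation therefore gives 31. If one counts only whole losses inside the ceiling, 30 just holds: 7/30 = 23.3% leaves 23, and 8/30 = 26.7% is above the ceiling. A target of 29 fails on either count.

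**Step 4: effect on power (assumed bases).** The section names no test, no sidedness and no standard deviation of the change, so power cannot be computed from the article alone. Two assumed bases give the scale:

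| Assumed basis | n = 23 | n = 22 |
|---|---|---|
| Two-sided paired t test, standardised effect 0.611 chosen so that n = 23 gives 80% | 80.0% | 78.1% |
| One-sided one-sample proportion test, 40% vs 65%, alpha 0.05 | 79.5% | 77.9% |

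The second row uses power = Phi{[0.25 x sqrt(n) - 1.645 x sqrt(0.40 x 0.60)] / sqrt(0.65 x 0.35)}. The loss is about 2 points on both bases.

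**The case against.** The strongest reply is that the text leaves room. The 25% is an upper limit, and 29 still yields 23 at any dropout up to 20.7%. The Abstract and Results give 29 as a floor, so enrolling 31 would already agree with them. Dropout is also not defined: someone who leaves the course early might still be retested and count for the primary endpoint.

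Part of this stands. It makes the practical consequence small, and the figure of 22 assumes that every dropout lacks the retest. It does not make 29 the right result of the stated inputs. A target derived from a ceiling should hold at that ceiling, and this one fails at 7 losses, inside it. A floor permits more recruitment but does not correct the derivation, and the Methods text gives no floor.

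A reader might infer something stronger in three ways, none of which the article supports:
- *That the trial may end with only 21 evaluable participants.* From 29, that takes 8 losses (27.6%), more than the plan allows for.
- *That 23 completers are unlikely.* If each of 29 participants has a 25% risk of dropping out, the chance of 23 or more completers is 39%. That treats the ceiling as everyone's risk. At assumed risks of 20%, 15% and 10% the chance is 64%, 87% and 98%. Even 31 enrolled reaches only 63% at a 25% risk, so much of the 39% is ordinary chance variation and not the inflation error.
- *That 78% is the plan's own power.* The article does not state the basis of its calculation, and its planned analysis is a Wilcoxon test. Any power figure here is an assumption.

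**Conclusion.** The point holds as a minor arithmetic error. At the plan's own ceiling of 25%, 29 enrolled leaves about 22 evaluable participants, not 23. The target covers up to 6 dropouts (20.7%), and the matching target for 25% is 31. The gap is about one evaluable participant, or two enrolled. If 23 gives 80% power, 22 gives about 78%.

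This assumes that a dropout has no usable post-course primary measurement and is not replaced. The design, endpoint and analysis are unaffected, and the point does not make the trial materially underpowered. Whether 23 is itself the right base is a separate question, not judged here.

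**What to change.** Correct the statement in the Abstract, the Sample Size Estimation section and the Results section so that all three agree. Any one of these will do:

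1. Keep 29 and say that it tolerates up to 6 dropouts (about 20%) while leaving 23 evaluable.
2. Keep 29 and the 25% ceiling, and say that about 22 evaluable participants are expected, with power slightly below 80%. If a power figure is printed, mark it as an assumption and name the test, the sidedness and the effect behind it.
3. Keep 23 evaluable at 25% dropout and set the target at 31. The Abstract and Results wording already allows this.

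Options 1 and 2 cost only wording; the stated dropout tolerance or power becomes slightly less favourable. Option 3 costs two more participants in a population that the authors describe as hard to recruit.

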### Data Collection

Data collection and databases are prepared for registration and data processing. Data at baseline include: age, living single vs cohabitant at home, in-home care services, mobility aids, social network, height, weight, smoking, and alcohol consumption.

### Statistical Analysis

Data comparisons of ranks before and after performances are calculated using Wilcoxon non-parametric test and optionally categorical variables with chi-2 test. Nonlinear correlations will be evaluated using the Spearman Rank correlation coefficient. Unused or incomplete data is not included in the statistical evaluation and is treated as missing data (ie, no calculations are made using such data). Lack of data is acceptable as long as an assessment of the primary endpoint is still possible. Data from participants that make it possible to assess the primary endpoint will be used as a minimum; however, we hope that data from all subjects can be used to evaluate secondary effect targets. *P* values of less than .05 will be considered significant.

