### Primary Hypothesis and Endpoint

It is our main hypothesis that participants will increase awareness of their surroundings, will improve navigating their surroundings, and will be able to experience a greater quality of life – including reduced symptoms of both fatigue and depression.

At the start of the intervention, standardized route training (mobility route training) is performed that participants must be able to perform independently, this intervention is also known as Mobility Assessment Course [2,6]. Mobility Assessment Course performance is the primary endpoint inspired by a similar trial, where the protocol was published, but currently the trial seems to have been cancelled [2]. On the route there are a number of targets (stars) that participants should locate. Investigators measure the number of targets ignored by any participant. Ability to perform correct target identifications by comparing how many targets participants identify before and after the intervention is the primary outcome measurement.

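### The incomplete-data rule does not exempt a test that was attempted but not finished; read literally, it deletes non-finishers from the route-time comparison, although the planned rank test could keep them

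*Protocol article*

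**What the plan says.** All references are to the protocol article.

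- **Statistical Analysis, exclusion rule:** "Unused or incomplete data is not included in the statistical evaluation and is treated as missing data". A bracket adds that such data enter no calculation. The word incomplete is not defined, and an attempted but unfinished test is not mentioned.
- **Statistical Analysis, tolerance and retention:** "Lack of data is acceptable as long as an assessment of the primary endpoint is still possible", and "Data from participants that make it possible to assess the primary endpoint will be used as a minimum".
- **Statistical Analysis, test:** "Data comparisons of ranks before and after performances are calculated using Wilcoxon non-parametric test".
- **Primary Hypothesis and Endpoint:** the outcome is a count of targets on the mobility route: "Investigators measure the number of targets ignored by any participant". At the start, "standardized route training (mobility route training) is performed that participants must be able to perform independently".
- **Secondary endpoints:** for speed, "Investigators measure the time spent by participants to complete the route". Faster is better provided that target identification has not fallen.
- **Blinding:** there is one treated group and no controls.

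**The concern.** The issue is people who come to the test and try it, not people who leave the trial. On a performance test, being unable to finish is a result, and it is the worst one. A rule that turns it into missing data makes the missingness depend on the outcome.

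The harm depends on the visit. Someone who finishes at baseline but not at the re-test has clearly got worse; deletion turns that into no information and favours the training. Someone who cannot finish at baseline but finishes afterwards is among the largest gainers; deletion removes that gain. No comparison arm under the same rule would offset either error, and the P value would not reveal it.

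The rule also sits badly with the chosen method. A rank test does not need the unfinished time, only the knowledge that it is slower than every finished one.

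**Working it through.** **1. Route time.** The endpoint is time to complete the route. A person who stops has no such time. The exclusion rule then applies, and a paired test loses the whole before/after pair. The retention sentence does not help, because it concerns data needed for the primary endpoint. The same reasoning covers any other timed performance test stopped because the person could not do it.

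**2. Primary count.** A person who stops has still found or missed targets up to that point, so a score exists if unreached targets count as not identified. The retention sentence could keep that person and the exclusion sentence could remove them. The article does not say which prevails.

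**3. Inputs for an illustration.** From Sample Size Estimation: "we expect participants to correctly identify 40% of the mobility targets at baseline", 65% at the re-test, and 23 evaluable participants. The expected gain is 65 − 40 = 25 points. Assumed, because the article gives neither: 1 to 3 unfinished routes, stopped halfway along evenly spaced targets, and an SD of change of 40 points. That SD is in line with the plan's own n: a two-sided paired comparison of means with 23 pairs, alpha .05 and 80% power implies 25 × √23 / (1.960 + 0.842) = 42.8 points.

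**4. Mean primary gain, unreached targets scored as not identified.**

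- Stop at re-test: 65/2 = 32.5%, a change of 32.5 − 40 = −7.5. Mean over 23 = [25(23 − k) − 7.5k]/23.
- Stop at baseline: 40/2 = 20%, a change of 65 − 20 = +45. Mean over 23 = [25(23 − k) + 45k]/23.

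| k stops | After deletion | Re-test stops kept | Baseline stops kept |
|---|---|---|---|
| 1 | 25.0 | 23.6 | 25.9 |
| 2 | 25.0 | 22.2 | 26.7 |
| 3 | 25.0 | 20.8 | 27.6 |

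**5. Chance of P<.05 with two stops.** Simulated two-sided Wilcoxon signed-rank test, 21 finishers with change ~ N(25, 40), several thousand trials per run.

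| Handling | Re-test stops | Baseline stops |
|---|---|---|
| Deleted | about 75% | about 75% |
| Kept, target-count score (primary) | about 67–70% | about 84–88% |
| Kept, extreme rank (as proposed for timed tests) | about 23–25% | about 89–91% |

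The ranges cover repeated runs, with the stopped person's change either fixed at −7.5 or +45 or scattered around it. The target-count score moves the re-test result much less because −7.5 is a small absolute difference and takes a low signed rank.

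**6. Direction under other assumptions.** Take SD 25 points per visit, correlation 0.3, n = 23, and delete the 1, 3 or 5 lowest scorers at one visit as non-finishers (1,500 trials per setting). With a true gain of 15 points, deletion at the re-test reports 16.4, 19.2 and 21.7; deletion at baseline reports 13.6, 10.9 and 8.6. With no true gain, the chance of a false finding of improvement (nominal 0.025) is about 0.05, 0.09 and 0.16 for re-test deletion, and 0.012, 0.004 and 0.002 for baseline deletion. This assumes that the non-finishers are exactly the lowest scorers.

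**The case against.** - **The text never calls an unfinished attempt incomplete.** True: this is a literal reading of an undefined term. For time the reading is hard to avoid, because no completion time exists to analyse.
- **The primary endpoint is safe.** A reader might infer that the worst routes are certain to vanish from the primary analysis. The article does not support that: the outcome is a count, a count exists without finishing, and "Data from participants that make it possible to assess the primary endpoint will be used as a minimum". Deletion there is possible, not certain. What stands is that the choice could be made after the results are seen.
- **Unfinished routes may be rare.** Nothing in the article predicts them. Its 35-metre mobility criterion allows assistance and wheelchairs, and the route length is not given, so the criterion does not show who can finish. The requirement of independent performance at the start makes baseline non-finishers less likely, and exclusion for new brain injury removes one cause of re-test failure. This limits the expected size; it does not supply a rule for the cases that occur.
- **Scoring of stopped tests belongs in an analysis plan or test manual.** For a detail left unstated, yes. Here the article states a rule, that such data enter no calculation, and that rule is the point.
- **Worst rank is a choice.** Stopping for fatigue or pain need not reflect visual search, and a paired rule needs a convention for stops at both visits. Both are fair. They are reasons to record why a test stopped and to fix the convention in advance.

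**Conclusion.** The point holds for route time and for any other timed performance test: as written, the rule deletes non-finishers for a reason tied to the outcome, although the planned test could rank them. Re-test deletion favours the training; baseline deletion, the less likely case, works against it. A reader might infer a bias always in favour of the training; the article does not support that.

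For the primary count the finding is an ambiguity. If such pairs were deleted, the illustrated shift is modest: 1.4 to 4.2 points too high for 1 to 3 re-test stops (25.0 − 23.6; 25.0 − 20.8), or 0.9 to 2.6 points too low for baseline stops (25.9 − 25.0; 27.6 − 25.0). With two stops, about 75% of trials reach P<.05 after deletion, against about 67–70% or 84–88% with the stops kept and scored.

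It is tempting to set 75% against roughly 24% as the effect on the primary endpoint. That contrast comes from extreme ranks, which suit timed tests only. It uses the target-gain figures as a stand-in, since the article gives none for time. Every size here rests on an assumed number of unfinished tests and an assumed SD.

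**What to change.** In Statistical Analysis, settled before results are seen:

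- Limit the exclusion to tests not attempted or lost for reasons unrelated to performance.
- For a route attempted but not finished, score targets not reached as not identified, over the full number of targets.
- Give an unfinished route time, or any other timed performance test stopped because the person could not do it, the slowest rank at whichever visit it occurs. In the paired test this is the largest worsening (re-test only) or the largest improvement (baseline only), with several such people tied. Non-completion at both visits is a tie, that is, no change.
- Report the number of unfinished tests at each visit.

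The cost is a few sentences and one tick-box on the test form (finished or stopped, with reason). The downside is that time is then reported as ranks or a median rather than a mean. Worst ranks also weigh heavily in a sample this small, which is why the counts per visit should appear beside the result.

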## Discussion

### Overview

To the best of the authors’ knowledge, this is the first time an investigation will evaluate the effects of Neuro Vision Technology complementary vision rehabilitation and we have received all necessary funding. Previously a similar trial was announced, but there have been no updates on progress for years and we assume that trial may never be finished [2]. According to the Australia and New Zealand Clinical Trials Register no updates have been received regarding the before mentioned trial since June 16 2010. Furthermore, our broad spectrum of secondary endpoints ensures a thorough examination of possible changes in quality of life, beyond previous investigations and case studies [3,5].

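### The main hypothesis takes in quality of life, fatigue and depression, but only route targets are primary and powered, and the .05 significance rule is not limited to that endpoint

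*Protocol article*

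**What the plan says.** Primary Hypothesis and Endpoint opens with a compound statement: "It is our main hypothesis that participants will increase awareness of their surroundings", that they will navigate better, and that they "will be able to experience a greater quality of life", "including reduced symptoms of both fatigue and depression". The same section then fixes a single primary outcome: "comparing how many targets participants identify before and after the intervention is the primary outcome measurement". Sample Size Estimation uses that outcome alone, with 40% of targets expected at baseline and 65% at 6 weeks after the course.

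Quality of life, fatigue and depression are measured only under Secondary endpoints. That section has 12 instruments. It starts with route time ("Time consumption in seconds and thus speed to complete the mobility route will be measured as a secondary endpoint") and a group of visual measures ("Visual functions will be estimated using the following five tests"), followed by MoCA, three depression and fatigue questionnaires, EuroQol-5D and the Barthel index. It also plans a comparison of right and left hemispheric lesions.

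The Conclusions of the Abstract say that quality of life and related cognitive gains are to be explored. The Overview of the Discussion says that "our broad spectrum of secondary endpoints ensures a thorough examination of possible changes in quality of life". Statistical Analysis ends with one rule for P: "values of less than .05 will be considered significant". It gives no order of testing and no adjustment, and does not limit the rule to the primary endpoint.

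**The concern.** The document gives quality of life two statuses: part of the main hypothesis in Methods, and a matter for exploration in the Abstract. Fatigue and depression are likewise inside the main hypothesis but are tested only through secondary scores, for which no power is stated.

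The unrestricted .05 rule makes this matter. With many secondary scores, some may fall below .05 by chance, and the text allows each to be reported as significant. Where such a score measures something named in the main hypothesis, a reader may take it as confirmatory. The Conclusion of the Discussion promises answers on efficacy, and with no control group there is no concurrent comparison against which to check a chance result on a self-report scale.

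**Working it through.** **The plan's own figure.** The plan gives no error rate for the secondary scores. Its only related figure is the sample size of 23 (alpha .05, beta .2, 40% versus 65%). A one-sample proportion formula comes close to it:

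n = [(z_α·√(p0·q0) + z_power·√(p1·q1)) / (p1 − p0)]², with p0 = .40 and p1 = .65.

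- One-sided .05: [(1.645 × .4899 + .8416 × .4770) / .25]² = 23.3.
- Two-sided .05: [(1.960 × .4899 + .8416 × .4770) / .25]² = 29.7.

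The stated 23 therefore fits a one-sided .05, although sidedness is not stated. Only the target percentages enter the calculation, so no other part of the main hypothesis is powered.

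**Count of secondary instruments (Secondary endpoints).** Route time 1; visual tests 5 (VFQ-25, TAP visual field, Behavioral Inattention Test, Rey-Osterrieth copy, King-Devick); MoCA 1; Major Depression Inventory, FSS-7 and MFI-20 3; EuroQol-5D 1; Barthel 1. Total 12. If the five MFI-20 domains were tested separately, the count would be 12 − 1 + 5 = 16.

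**Chance of at least one false significant result**, if no secondary outcome changes and each test is at .05. Under independence this is 1 − .95^k:

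- 12 instruments: 1 − .95^12 = .460, with 12 × .05 = 0.6 false positives expected.
- 16 scores: 1 − .95^16 = .560.
- The four instruments tied to the main hypothesis (EuroQol-5D, FSS-7, MFI-20, Major Depression Inventory): 1 − .95^4 = .185.

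**Effect of correlation.** The documents give no correlations, so a range is assumed. In a simulation of 12 equally correlated normal statistics (200,000 draws, two-sided .05), the chance was:

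- .40 at a correlation of .3
- .32 at .5
- .23 at .7

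**Effect of direction.** If the tests are two-sided, a false claim of improvement has probability .025 per test. Under independence that gives 1 − .975^12 = .26 for 12 instruments and 1 − .975^4 = .10 for four.

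**Primary endpoint.** One outcome tested once, at the 6-week time point named in Sample Size Estimation, keeps its .05 whatever is done with the secondary scores.

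**The case against.** The plan already has most of a hierarchy. One primary outcome is named, it alone is powered, and it determines which participants' data are usable; everything else is labelled secondary. Adjustment of secondary endpoints is often left to an analysis plan, and none is shown here. This stands in part: the lack of an adjustment method would not be a finding in itself. But the article states a definite rule without limits, directly after a sentence about secondary effects, and it contradicts itself on the status of quality of life. Both are in the text.

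Three stronger readings are tempting and are not supported.

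- A reader might infer that one quality-of-life, fatigue or depression score below .05 would establish the main hypothesis. The hypothesis is worded as a conjunction, so taken literally every part must hold. That is a stricter requirement than a single test at .05, not a looser one. The risk is over-reading of individual secondary results, not proof of the whole hypothesis by one of them.
- A reader might infer that the primary test has an inflated error rate. It does not.
- A reader might multiply 16 scores by two re-tests and quote 1 − .95^32 = 81%. This assumes that every score and every MFI-20 domain is tested, independently, at both re-tests. The article does not say so: it also describes testing of the endpoints at baseline and end of study, and notes that the MFI-20 general domain can serve as the overall fatigue measure.

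It is also fair that most of the 12 instruments do not measure quality of life, fatigue or depression. For those parts of the hypothesis the four-instrument figure is the relevant one.

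**Conclusion.** The point holds as one about what the trial may conclude. The main hypothesis is wider than the only primary and powered outcome, it disagrees with the Abstract on quality of life, and the .05 rule lets any secondary result be called significant.

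The size is a 46% chance of at least one false significant result across 12 instruments under independence, and about 23% to 40% at assumed correlations of .7 to .3. For the four instruments that bear on quality of life, fatigue and depression it is 18.5% under independence. These figures assume that no secondary outcome truly changes and that each instrument gives one test at .05. Positive correlation lowers them, and counting only false improvements in two-sided tests lowers them further. The analysis of the primary endpoint is unaffected.

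**What to change.** In Primary Hypothesis and Endpoint, restate the main hypothesis as an improvement in the number of targets identified at the 6-week re-test, the time point that the sample size already uses. Move quality of life, fatigue and depression to the secondary aims.

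In Statistical Analysis, state that only this test, at .05, supports a confirmatory claim. Report quality of life, fatigue, depression and all other secondary scores as exploratory estimates with 95% confidence intervals, in line with the Abstract.

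If a confirmatory secondary claim is wanted, name one score per domain in advance and adjust across them, for example with Holm. That is one option among several and is not required.

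The change is to wording only and leaves the sample size for the primary endpoint as it is. The cost is that fewer secondary results may be called significant.
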